#### Exclusion criteria

2.3.3

Participants will be excluded if any of the following apply:Participants who have received medication or related treatments for LBP or discomfort within the past 7 days, including treatment at medical (Western medicine) or Korean medicine institutions.Participants with a history of lumbar spine surgery within the past 3 months.Participants who developed lumbar sprain due to trauma (e.g., traffic accident, fall, or contusion) within the past 3 months.Female Participants who are currently pregnant or who have given birth within the past 6 months.Participants with renal or endocrine disorders accompanied by symptoms such as edema.Participants currently taking antithrombotic agents (including anticoagulants or antiplatelet medications).Participants with cognitive impairment that makes it difficult to understand the study procedures or provide voluntary informed consent.Participants currently taking psychiatric medications for conditions such as depression.Participants deemed unsuitable for participation at the discretion of the investigator (e.g., refusal to follow instructions, safety concerns).

#### Dropout criteria

2.3.4

This study involves a single intervention (Visit 1), and participants who complete this procedure will not be classified as dropouts. The follow-up assessment conducted 24–36 h later serves as an additional evaluation; therefore, lack of response to this assessment does not constitute withdrawal, and participation will still be considered valid. Dropout criteria apply only under the following circumstances:

*Withdrawal of consent*: If the participant or their legal representative requests termination of study participation or withdraws informed consent at any time.*Inability to perform the procedure*: If the participant’s medical or physical condition changes before the intervention, and the investigator determines that performing ultrasound-guided pharmacopuncture is no longer safe.*Unexpected medical issues following the procedure*: If a significant adverse reaction or medical complication occurs during or after the intervention, and continued participation is considered inappropriate.*Investigator decision*: If the investigator determines that continued participation jeopardizes participant safety, compromises data integrity, or undermines the ethical conduct of the study.

Non-response to the 24–36-h follow-up assessment alone does not constitute dropout; such missing data will be treated as simple missing values during analysis.

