**Figure 2 fig2:**
[figure not shown]
Comparison of the two magnetized needle types used in this study (26G × 60 mm and 25G × 100 mm).

All four participating clinical sites routinely use both types of needles in daily practice, depending on actual clinical circumstances. For the purpose of comparative analysis, two sites will be designated to contribute only cases treated with short needles, while the other two sites will contribute only cases treated with long needles. This approach represents a site-level data extraction scheme, rather than a randomized allocation process, and is designed to enable comparative analysis of procedures performed in routine clinical practice without modification of standard patient care.

The study procedures consist of three stages: screening, the treatment visit (Visit 1), and post-procedure follow-up at 24 to 36 h. After providing written informed consent, participants undergo screening, during which demographic characteristics and relevant medical history are collected, and eligibility is assessed based on predefined inclusion and exclusion criteria. Participants who meet all eligibility criteria proceed directly to Visit 1, during which the ultrasound-guided pharmacopuncture intervention and all corresponding study assessments are conducted.

During Visit 1, all enrolled participants undergo a single ultrasound-guided PDRN pharmacopuncture procedure following a standardized protocol. Prior to the intervention, baseline assessments are conducted, including Numerical Rating Scale (NRS) scores for LBP and radiating leg pain, lumbar ROM, the Oswestry Disability Index (ODI), and the Patient-reported Percentage Pain Reduction(PRPPR) score. After the baseline evaluation, the practitioner identifies the interfascial QPI space using high-resolution ultrasonography and then performs the injection using a magnetically guided needle system, administering 1–2 mL of the PDRN pharmacopuncture solution.

The procedure is performed using an in-plane needle approach, enabling real-time visualization of the needle trajectory and tip through ultrasound imaging combined with a magnetic needle-tracking system. Both groups receive the same injection technique and target the same anatomical site; however, the SNG uses a 26G × 60 mm needle, while the LNG uses a 25G × 100 mm needle. All other procedural variables remain consistent across groups.

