#### Ultrasound-guided interfascial injection procedure at the QPI space

2.4.1

The L3 spinous process is initially identified using an ultrasound device (AcuViz Pocket).The probe is then rotated 90 degrees to obtain a transverse view and visualize the transverse process of L3.The probe is moved slightly cranially until the PM, previously obscured by the transverse process, becomes visible.The probe is adjusted until the medial border of the QL aligns approximately with the lateral border of the IC muscle.After identifying the IC, QL, and PM muscles, the probe is stabilized once a peristaltic bowel movement is observed lateral to the PM, indicating the appropriate depth and confirming the anatomical landmarks.The skin over the planned needle entry site is thoroughly disinfected over a sufficiently wide area.Using an in-plane approach, the magnetic pharmacopuncture needle is advanced toward the medial border of the QL muscle and positioned within the interfascial plane. The injectate is then slowly administered to facilitate natural spread toward the PM fascia.During the procedure, the patient may experience transient neural sensations, such as radiating tingling, warmth, numbness, or a relieving sensation in the lower limb.After completing the injection, the needle is withdrawn, and hemostasis is achieved if bleeding occurs, followed by the application of a sterile dressing.The patient is instructed to stand and perform gentle lumbar flexion, extension, and rotation to assess any changes in symptoms or adverse reactions (Figure 3).

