#### Statistical analysis

2.6.2

All statistical analyses will be performed using R software (version 4. X. X; R Foundation for Statistical Computing, Vienna, Austria). All tests will be two-tailed, with statistical significance defined as *p* < 0.05. Continuous variables will be summarized as mean ± standard deviation or median with Interquartile Range (IQR), depending on the data distribution. Categorical variables will be presented as frequencies and percentages.

For the primary outcome, changes in NRS scores will be analyzed according to the data distribution. Between-group comparisons will be performed using an independent *t*-test if the normality assumption is satisfied; otherwise, the Wilcoxon rank-sum test will be used. Within-group changes will be assessed using a paired *t*-test or the Wilcoxon signed-rank test, depending on whether the data meet normality assumptions.

For the secondary outcomes, changes in lumbar ROM from baseline will be analyzed using the same statistical methods applied to the primary outcome. Between-group comparisons will be conducted using an independent *t*-test or the Wilcoxon rank-sum test, while within-group comparisons will be analyzed using a paired *t*-test or the Wilcoxon signed-rank test, depending on data normality.

The ODI will be categorized into predefined functional disability levels, and differences in distribution between groups will be analyzed using the Chi-square test or Fisher’s exact test, as appropriate.

PRPPR will be assessed immediately after treatment and again at 24–36 h post-intervention. Between-group comparisons will be conducted using an independent *t*-test or the Wilcoxon rank-sum test, while within-group comparisons will be analyzed using a paired *t*-test or the Wilcoxon signed-rank test, depending on the data characteristics.

In addition, procedural characteristics and usability-related variables associated with needle length—including deep-layer reach success rate, number of insertions, procedure time, and operator usability score—will be summarized using descriptive statistics. When appropriate, exploratory between-group comparisons will be conducted using the Mann–Whitney U test or the Chi-square test. These analyses will serve as supportive reference analyses and will not directly influence the interpretation of the primary clinical outcomes.

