The interfascial plane of the lumbar region can present varying levels of technical difficulty depending on factors such as body habitus (including BMI and muscle thickness), probe–needle alignment, acoustic properties, and anatomical variations. Anatomical and imaging studies indicate that the target layer is typically located at a depth of approximately 4–6 cm or more from the skin surface (32). Given this depth, conventional 50–60 mm needles may provide limited access or an insufficient safety margin in patients with increased soft tissue thickness. In contrast, anesthesia literature shows that 80–100 mm block needles are routinely used for similarly deep interfascial approaches, such as QL or Erector Spinae Plane (ESP) blocks (33–37). However, within Korean medicine clinical practice, systematic validation of long-needle use—particularly regarding safety, reproducibility, and ultrasound visibility—has been limited, resulting in selective or restricted adoption in real-world settings. Accordingly, the design of the present study holds both methodological and clinical relevance by addressing this gap and evaluating the feasibility of long-needle application in ultrasound-guided interfascial pharmacopuncture.

This study has several methodological strengths, including its prospective design, needle-length comparison framework, multicenter real-world data collection, and incorporation of practitioner usability assessments. Notably, the study was designed to collect not only clinical response outcomes but also procedural variables such as needle handling experience, perceived technical difficulty, and confidence in reaching the target plane. This approach enables exploration of the relationship between therapeutic outcomes and procedural experience. Furthermore, conducting the study in a real-world outpatient clinical setting enhances the applicability of the findings, as it reflects variability in patient characteristics, procedural accessibility, and the operator learning curve. These features contribute to the study’s potential value for future clinical implementation and the development of educational frameworks.

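### Inclusion depends on the needle the patient ends up being treated with, so a short-needle attempt that is abandoned or finished with the other needle can leave the comparison after treatment

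*Protocol article*

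**What the plan says.** **Group and inclusion.** Section 2.1 (Study design) has two sites contribute only short-needle cases and the other two only long-needle cases. It also states that "All four participating clinical sites routinely use both types of needles in daily practice". The last item of section 2.3.2 (Inclusion criteria) turns this into an eligibility condition: treatment with the long needle at two named clinics, or with the short needle at the other two.

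**Completion and dropout.** Section 2.3.4 (Dropout criteria) says that "participants who complete this procedure will not be classified as dropouts" and does not define completion. The list of exceptions is closed: "Dropout criteria apply only under the following circumstances". The item on inability to perform the procedure begins "If the participant’s medical or physical condition changes before the intervention", so it does not cover a technical failure after insertion. The investigator-decision item is wider and applies where "continued participation jeopardizes participant safety, compromises data integrity, or undermines the ethical conduct of the study".

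**Procedure.** Section 2.4.1 describes the successful path only, with the needle "positioned within the interfascial plane. The injectate is then slowly administered".

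**Expected reach.** The Discussion says that "the target layer is typically located at a depth of approximately 4–6 cm or more from the skin surface". Both it and the Introduction warn that needles of about 60 mm may not reach deep targets reliably.

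**Measurement.** Section 2.1 records tip arrival and visible injectate spread, and reassesses NRS, PRPPR and ROM straight after the procedure. Section 2.6.2 (Statistical analysis) summarises "deep-layer reach success rate, number of insertions, procedure time, and operator usability score" by needle length, as supportive analyses.

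**The concern.** The study asks whether needle length affects access to the plane and, through it, immediate pain relief. A short needle that cannot reach the plane is a result on that question. If the needle finally used, or the fact that treatment was finished, decides who is included, that result can remove the patient from the data.

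This selection would happen after treatment starts, would depend on how the procedure went, and would fall mainly on the short-needle group. The short-needle patients left would be those with more accessible targets. Their reach rate would look better than the needle deserves, and the NRS comparison would shift in the same direction.

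**Working it through.** **Step 1. Where each kind of failure goes under the text as written (short-needle site).**

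| What happens after insertion | 2.1 and 2.3.2 (needle used) | 2.3.4 (completion, dropout) | Likely status |
|---|---|---|---|
| Injectate given, but outside the plane | Treated with the short needle: included | Procedure done, not on the dropout list | Stays in, reach recorded as failed |
| Finished with the 100 mm needle | Not clearly a short-needle case, and not at a long-needle site | Not on the list unless the investigator decides so | Can fail inclusion after treatment |
| Abandoned, nothing injected | Not clearly treated with either needle | Completion undefined; discretionary route open | Can fail inclusion or be dropped |

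The first row is reasonably settled. The other two are not, and two sites could handle the same event differently.

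**Step 2. Is a reach failure plausible, and in which group?** Inputs from the article: needle lengths of 60 and 100 mm, and a target at about 4–6 cm or more. The article gives no insertion angle, so the angles here are assumptions. Maximum depth = length × sin(angle to the skin), ignoring tissue compression:

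- 45°: 60 × 0.707 = 42 mm; 100 × 0.707 = 71 mm
- 60°: 60 × 0.866 = 52 mm; 100 × 0.866 = 87 mm

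On an oblique path the short needle covers only part of the stated depth range, while the long needle covers 6 cm at both angles. This agrees with the article's own expectation. It does not give a failure rate.

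**Step 3. Effect on the reach rate (9 failures in 60 assumed).**

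- All started procedures: 51/60 = 85%
- Failures left out: 51/51 = 100%

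**Step 4. Effect on the primary comparison (assumed inputs).** Let f be the share of short-needle patients who fail and are removed. Let g be the NRS points by which they improve less than the others, whose mean reduction is m. The mean over all short-needle patients is (1 − f)·m + f·(m − g) = m − f·g. After removal it is m. A long-needle advantage therefore shrinks by f × g. I take g from 1 to 2.74; the upper end is the treatment-group mean reduction quoted in section 2.6.1, as if failures did not improve at all. The planning difference there is 2.74 − 1.76 = 0.98.

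| f | f × g (g = 1 to 2.74) | Share of 0.98 |
|---|---|---|
| 10% | 0.10 to 0.27 | 10% to 28% |
| 20% | 0.20 to 0.55 | 20% to 56% |
| 30% | 0.30 to 0.82 | 31% to 84% |

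For a patient whose injection was successfully finished with the long needle, g could be close to zero. The NRS bias would then be small, but the reach-rate bias would remain.

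**Step 5. Is it a sample-size problem?** The plan's figure reproduces. With d = 0.56, two-sided 0.05 and 80% power, the t-test solution is 51.03, hence 52 per group and 104 in total (power 80.7%). Then 104/0.9 = 115.6, so 116; the target of 120 covers it. With 60 long-needle patients and 54, 48 or 42 short-needle patients, power at d = 0.56 is 84%, 82% or 79%. The issue is bias, which more recruitment would not cure.

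**The case against.** The strongest reply is that the text does not exclude failures. Section 2.3.4 does not tie completion to reaching the plane, and its dropout list does not mention a failed reach. Section 2.1 reassesses NRS, PRPPR and ROM after the procedure with no condition on reach. A planned reach success rate presupposes that failures are counted. This stands, and it settles the off-target injection: that patient most naturally stays in.

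A reader might go further and infer that any undelivered procedure is neither completed nor a dropout, that no post-procedure NRS is due, or that the plan computes reach over completed procedures only. The documents support none of these. Completion is undefined, the investigator-decision item could take in such a case, the reassessment is unconditional, and no denominator is stated.

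Two further replies carry weight. Eligibility is assessed before the intervention, so the needle criterion could be read as the intended needle; but sections 2.1 and 2.3.2 are worded by treatment received. Conversion during a procedure is also never described. It is only foreseeable, because every site uses both needles according to circumstances.

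Finally, analysis sets may sit in a statistical analysis plan that is not shown, and section 2.3.6 refers data collected before withdrawal to the protocol and that plan. But such a plan cannot readily restore patients whom the eligibility wording excludes, or an immediate NRS that was never taken.

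**Conclusion.** The point holds for abandoned and converted procedures. Followed as written, the needle-used rule in sections 2.1 and 2.3.2 can remove these patients after treatment, and section 2.3.4 leaves the rest to discretion. The article itself expects limited reach mainly with 60 mm needles, so the loss would be selective.

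The size is unknown, because the documents give no failure or conversion rate. The 85% versus 100% reach rate and the 0.10 to 0.82 NRS points are illustrations that rest on assumed failure shares, an assumed difference in response, and removal of every failure. If such events are rare, or converted patients respond as well as the others, the effect on the primary outcome is small. No stated figure in the plan is wrong.

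**What to change.** - **Sections 2.1 and 2.3.2:** set the group by the site-designated needle first inserted, whatever needle finishes the procedure.
- **Section 2.3.4:** count a participant as treated from first needle insertion, and state that abandonment or a change of needle is not in itself a dropout.
- **Data collection:** take the immediate NRS, ROM, PRPPR and adverse events from everyone with an insertion. Add two CRF fields, procedure abandoned and second needle used. Tip arrival and injectate spread are already recorded.
- **Section 2.6.2:** keep these participants in the primary comparison under the first needle, and use all started procedures as the denominator of the reach success rate.

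How the operator proceeds when the plane is not reached is for the sponsor to settle; this change only fixes how such cases are counted.

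The cost is a few sentences and two tick boxes, with no extra visit. The downside is that the comparison will include incompletely delivered injections, and the short-needle figures may look less favourable.

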During the procedure, performance-related indicators are recorded, including the number of needle insertions, total procedure time, confirmation of needle-tip arrival at the deep target layer (QPI space), and visualization of the hypoechoic spread during injectate delivery. All ultrasound images and needle-tracking log data are stored for subsequent analysis.

Immediately after the procedure, pain intensity (NRS), PRPPR, and ROM are reassessed. Additionally, the operator completes a usability questionnaire to evaluate needle visibility, tracking stability, handling comfort, confidence in target engagement, perceived procedural workload, and overall satisfaction. Any immediate adverse events occurring at this time point are documented in detail.

Follow-up assessments are conducted via telephone within 24 to 36 h after the procedure. During this contact, changes in pain intensity (NRS), PRPPR, functional status in daily activities, and the presence of any delayed adverse events are evaluated. All collected data are recorded using institution-specific Case Report Forms (CRFs) and included in the final analysis after de-identification. A summary of the study procedures is presented in Table 1.

**Table 1 tab1:** Summary of study procedures and assessment timeline.

Study procedure	Period		
	Screening*	Visit 1	F/U^†^
	-1D^‡^	Baseline (0)	~1D
Explanation of the study and obtaining consent	○		
Determination of inclusion/exclusion criteria	○		
Demographic survey^a^	○		
Medical history investigation^b^	○		
ODI (Baseline)^c^		○	
NRS (Pre-/Post-intervention, Day 1)^d^		○	○
PRPPR (Post-intervention, Day 1)^e^		○	○
ROM (Range of Motion) (Pre-/Post-intervention)^f^		○	
Intervention (Short needle vs. Long needle)		○	
Adverse event assessment^g^		○	○

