#### Management of early termination and dropout

2.3.6

In cases of early termination or participant dropout during the study, the investigator will document the reason and timing of withdrawal in both the CRF and the participant’s medical record. If the withdrawal is suspected to be related to an adverse event, follow-up contact will be made to assess the participant’s clinical status. When an adverse event is confirmed, appropriate medical care will be provided in accordance with the clinical guidelines of each participating institution.

If the study is terminated prematurely at either the institutional or overall study level, the principal investigator will compile all collected study materials—including participant records and study documents—up to the point of termination and report them to the IRB and the relevant institution. All data and materials will then be stored or disposed of in accordance with institutional policies and IRB requirements.

Participants who discontinue the study will not be re-enrolled. The inclusion of data collected prior to withdrawal in the final analysis will be determined according to the study protocol and the predefined statistical analysis plan. Since the follow-up assessment at 24–36 h is considered an additional exploratory endpoint, the absence of follow-up data alone will not be classified as dropout. Non-responses at this time point will be treated as missing data and handled accordingly in the analysis.

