If significant baseline differences are identified between the two groups and these variables are considered potentially related to the outcome measures, they will be treated as possible confounding factors. In such cases, subgroup analyses or multivariate analyses (e.g., ANCOVA or multiple regression models) will be conducted. Adjusted effect sizes with corresponding 95% confidence intervals will be reported to improve the interpretability and accuracy of the findings.

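### The 24–36 h PRPPR comparison uses only patients who answer the call, although the immediate scores scheduled for all treated patients would support a less fragile analysis

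*Protocol article*

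**What the plan says.** Section 2.3.4 of the protocol article separates non-response to the follow-up call from dropout and adds that "such missing data will be treated as simple missing values during analysis". Section 2.3.6 repeats the rule without naming a method: "Non-responses at this time point will be treated as missing data and handled accordingly in the analysis". The same section gives the time point its status: "Since the follow-up assessment at 24–36 h is considered an additional exploratory endpoint".

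Section 2.6.2 then sets the analysis: "PRPPR will be assessed immediately after treatment and again at 24–36 h post-intervention". The tests for both times follow: "Between-group comparisons will be conducted using an independent *t*-test or the Wilcoxon rank-sum test, while within-group comparisons will be analyzed using a paired" t-test or its signed-rank counterpart. The only provision for adjustment opens with "If significant baseline differences are identified between the two groups", so it responds to baseline imbalance and not to missing outcomes.

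On data collection, section 2.1 states "Immediately after the procedure, pain intensity (NRS), PRPPR, and ROM are reassessed" and, for the later time, "Follow-up assessments are conducted via telephone within 24 to 36 h after the procedure". Table 1 shows the same schedule: NRS and PRPPR are due after the procedure and again at Day 1.

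**The concern.** A two-sample test at 24–36 h can use only values observed then, and the paired test only complete pairs. Read with the rule in 2.3.4, a patient who does not answer leaves both analyses. The group difference among responders estimates the difference among all treated patients if answering is unrelated to pain relief, and nearly so if it depends on relief in the same way and at the same rate in both groups.

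There is some reason to doubt the second condition. Two clinics supply only short-needle cases and two only long-needle cases (2.1, 2.3.2), so any difference between clinics in reaching patients is also a difference between needle groups. The 10% allowance in 2.6.1 is for dropout, and 2.3.4 says non-response is not dropout, so that figure does not describe the loss expected at the call.

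The 24–36 h scores are the only data on pain after the clinic visit. A difference in who answers could create or mask a group difference there. The immediate PRPPR and NRS are likely to predict the later score and are scheduled for every treated patient, yet the stated tests make no use of them for those who do not answer.

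**Working it through.** **The plan's own figure.** The only calculated figure is the primary-outcome sample size. With d = 0.56, two-sided 0.05 and 80% power, the normal approximation gives 2 × (1.96 + 0.8416)² / 0.56² = 50.06, so 51 per group. The exact t-test calculation gives 51.03, so 52 per group and 104 in total, as stated. With 10% dropout, 52 / 0.9 = 57.8, so 58 per group or 116, which the target of 120 covers. None of this depends on the follow-up call.

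**What the two rules imply together.**
- Rule for non-response: simple missing values (2.3.4), no method named (2.3.6).
- Tests for PRPPR: two-sample between groups, paired within group (2.6.2).
- Covariates, imputation or joint model for missing outcomes: none stated.
- Result: an available-case comparison at 24–36 h.

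**Size of a possible bias.** For each group, let the shift be the mean standardised immediate score among responders minus that among all treated patients. If non-response depends only on the immediate score, then

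bias of the responders-only difference ≈ correlation × SD × (shift in one group − shift in the other).

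The group size of 60 is from 2.6.1. All other inputs are assumptions, because the documents give none: mean PRPPR 50, SD 25, correlation 0.6 between the two times, no true difference, and non-response logistic in the immediate score with a log-odds slope of 1 per SD where a relation is assumed. With 4,000 simulated trials per scenario, the absolute bias is:
- random non-response, or the same mechanism and rate in both groups: about 0
- 10% versus 25% non-response, same slope: 1.8 points
- 10% versus 30%, same slope: 2.3 points
- 20% in each group, related to relief in one group only: 2.5 points
- 20% in each group, opposite directions: 5.1 points

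As a check, two equal and opposite shifts should double the one-group bias: 2 × 2.5 = 5.0, against 5.1.

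**Range.** Varying the correlation over 0.5 and 0.7, non-response at the average score over 10%, 20% and 30%, and the true difference over 0 and 10 points gives:
- random: about 0
- same mechanism in both groups: about 0 with no true difference, and up to 1.1 points towards zero with a true difference of 10
- one group only: 1.2 to 4.9 points
- opposite directions: 2.6 to 9.7 points

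**Against the precision.** The standard error is about 5 points. A bias of 2.3 is 2.3 / 5 = 0.46 standard errors, so the two-sided error rate is Φ(−1.96 + 0.46) + Φ(−1.96 − 0.46) ≈ 0.067 + 0.008 = 7.5% instead of 5%. For 1.8 points (0.36 standard errors) it is about 6.5%, and for 5.1 points (1.02) about 17.5%.

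**Using the immediate score.** Regressing the later score on the immediate score within each group and predicting at the mean of all treated patients in that group brings the bias to within about 0.3 points in every scenario, with essentially the same standard error. This result is partly built in, because non-response was generated from that same score.

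**The case against.** The strongest objection is that handling of missing data belongs in the statistical analysis plan, which is not shown. The sentence in 2.3.4 mainly classifies non-response as not being dropout, 2.3.6 names no method, and no section rules out imputation. This is a fair limit, but it does not dispose of the point. The article does state a rule and does fix the tests, and those tests can use only observed values. A plan that used the immediate scores would have to depart from that wording.

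Three stronger readings are tempting, and the documents do not support them.
- A reader might infer that each clinic makes its own calls, so that response must differ by group. Section 2.1 says only that follow-up is by telephone, and 2.9 adds mobile contact. Institution-specific case report forms make site-run calls plausible, no more.
- A reader might infer that the immediate score would remove the bias. It removes only the part that the observed scores explain. If patients do not answer because of how they feel at 24–36 h, some bias stays.
- A reader might infer that 2.3.6 and 2.6.2 contradict each other on status. They can be reconciled: 2.5.2.3 makes PRPPR a secondary outcome to capture the immediate effect, and 2.3.6 calls the later call exploratory. What is missing is a label in 2.6.2.

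It also stands that the size is assumed and mostly small, that the documents give no reason to expect opposite mechanisms in the two groups, and that the limitations in section 3 already disclaim sustained effects and acknowledge possible selection bias from site-based allocation.

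**Conclusion.** The point holds as a low-priority improvement. As written, the plan gives a responders-only comparison of PRPPR at 24–36 h and leaves unused the immediate scores due from all treated patients; a withdrawal or complication straight after the procedure would be a rare exception.

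The bias is possible, not shown. At a correlation of 0.6 it is about 0 to 2–3 points on the 0–100 scale in moderate scenarios, roughly half a standard error. It reaches 5 points or more only if relief drives non-response in opposite directions in the two groups. These figures rest on the assumed SD, correlation, slope and non-response rates. The primary outcome and the sample size are not affected.

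**What to change.** In 2.3.4, 2.3.6 and 2.6.2, replace the simple-missing rule with the following.
- Analyse PRPPR at both times in one repeated-measures model with group, time and group by time and an unstructured covariance, including all treated patients whether or not they answered the call.
- Use the immediate NRS in the same way for any between-group analysis of NRS at 24–36 h, since that score faces the same non-response.
- Report the number and reasons for non-response by group and by clinic. Section 2.7 already requires reasons for missing data to be recorded, so only the tabulation is new.
- Label the 24–36 h PRPPR result exploratory in 2.6.2, in line with 2.3.6.
- Add one simple sensitivity analysis in which non-responders' later scores are shifted by a stated amount, separately by group.

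The cost is wording and one standard model on data already scheduled, with no loss of precision in the simulations. The downside is that the model assumes non-response is explained by the observed scores. That is weaker than the present assumption but still an assumption, hence the sensitivity analysis. The article states that no participant had been recruited at submission; if that is still so, the change can be made before any data are seen.
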